### Intervention

Adolescents assigned to the intervention group receive a PlayStation®Move upgrade package to play active games on a PlayStation3 console. PlayStation®Move uses a handheld motion controller wand and a motion-capture PlayStation®Eye camera that tracks the position, and inertial sensors in the wand to detect its motion. In this way every movement of the player is mimicked on-screen in the game. Although, there are multiple active game systems (such as Nintendo Wii, Dance Dance Revolution, Microsoft Xbox Kinect, PlayStation2®EyeToy) available on the market, the PlayStation®Move was chosen for the current study for several reasons. First, a survey study showed that the PlayStation was the most frequently owned game console among 12–16 year old adolescents [19]. So by choosing an application that is compatible with the PlayStation, we optimize the chances for recruiting sufficient participants. Second, the active game system for the PlayStation is one of the newest on the market at time of the study, making use of the most sophisticated technology, and may be more affordable (around €50) than other consoles or active game upgrades (e.g. Microsoft Kinect (around €135)).

As mentioned in the introduction previous studies showed that attention should be paid to (ongoing) participation in active game play, therefore we include several motivation enhancing intervention elements. Since variation in games is important [22,46,47], families receive four active Move games (Sport Champions, Move Fitness, Start the Party and Medieval Moves) at the start of the study and two more (Dance Star Party and Sorcery) after four months. Social and family play is important [22,44], and we provide two controllers to promote playing together with family and friends. Further, research has shown that providing instruction to use the active games seems an important addition to providing the games for physical activity promotion [46,48], therefore we explicitly encourage participants at each contact moment to substitute non-active gaming with active gaming as much as possible but at least one hour per week. One hour per week corresponds with approximately 70 kcal (representing the energy imbalance that can result in excessive weight gain) [43], and was regarded as a feasible change.

Adolescents in the control group are asked to continue their normal gaming behavior. They receive a PlayStation Move starters pack at the end of the study as an incentive for their participation. Further, they receive a small gift (e.g. magazine, lanyard, pen) as an incentive after participation at each measure moment.

### Measurements

#### Adolescents’ anthropometrics (T_0_, T_4m_, T_10m_) (primary outcomes)

Adolescent’s anthropometric measures: height, weight, waist and hip circumferences and skinfolds thickness are performed at T_0_, T_4m_ and T_10m_ on pre-scheduled days at central places in the same four cities where we recruited the participants. These measurements take place at a site close to where the participants live (a museum, school or soccer stadium). Adolescents who are incapable to visit during the pre-scheduled days are measured at home. Trained research assistants conduct the measurements in an accurate manner according to a standardized protocol.

Height is measured to the nearest 0.1 cm using a Seca type 214 stadiometer with adolescents standing on bare feet and their head in the Frankfort plane. Weight is measured on bare feet with a calibrated electronic scale (SECA) with an accuracy of 0.1 kg. Adolescents are allowed to wear light indoor clothing, such as a t-shirt and shorts/short pants, and are asked to remove belt or any other heavy objects of use such as phone, keys or wallet. BMI (kg/m^2^) is calculated by dividing weight (kg) by height squared (m^2^). Next, BMI-SDS is determined using the data from the fourth Dutch growth study among children of 1997 as reference [3] employing the Growth Analyser software (https://www.growthanalyser.org/). Waist and hip circumference are measured with a tape measure (brand Jobst) to the nearest 0.1 cm. For waist circumference we also determine the SDS values using the same reference group and software as for BMI. Skinfolds are measured with an accuracy of 0.2 mm using four-site skinfold measures (triceps, biceps, subscapular and suprailiac) with a Harpenden skinfold calliper [49]. For hip circumference and skinfold thickness valid Dutch reference data to calculate SDS scores are not available.

At least two readings of each measurement (weight, height, waist/hip circumference and skinfolds) are obtained to deal with intra-observer variability, and the mean of the two measurements is used for analyses. If the two readings differ more than 1 cm for height, more than 0.2 kg for weight, more than 1 cm for waist and hip circumference, more than 1 mm for skinfolds, a third measurement is taken. In case of three measurements, the outlier of the three will be excluded.

#### Self-reported measures

Online questionnaires (made with the online tool NETQ http://www.netq-enquete.nl/nl) are emailed to the adolescents at T_0_, T_1m_, T_4m_ and T_10m_. The questionnaires assess demographics birth date, sex, educational level (pre-vocational; higher continued education; pre-university) and country of birth. Also active and non-active gaming behavior, other energy balance related behaviors, game consoles/application owned and game companions are assessed in the questionnaires (Table 2). Among the adolescents in the intervention group a process evaluation is conducted. Several process evaluation questions are added in the questionnaire of the intervention group at T_1m_, T_4m_, T_10m_ (Table 3). Furthermore, adolescents in the intervention group are asked to report their use of the Move games over the entire ten-month period using a calendar format.

**Table 2 T2:** Gaming aspects and behavior, physical activity, sedentary and dietary behavior assessed in questionnaires

	**Items and answering categories**	**Instrument/source**
**Gaming aspects and behavior**		
Time spent non-active gaming	*1. How often do you play non-active games on weekdays? (1–5 days a week)*	De Jong et al., 2013 [50]
	*2. How long per day do you play non-active games on a weekday? (… hours; … minutes)*	
	*3. How often do you play non-active games on weekend days? (1–2 days a week)*	
	*4. How long per day do you play non-active games on a weekend day? (… hours; … minutes)*	
Time spent active gaming	*1. How often do you play active games on weekdays? (1–5 days a week)*	De Jong et al., 2013 [50]
	*2. How often do you play active games on weekend days? (1–2 days a week)*	
	*3. How often do you play active games on weekend days? (1–2 days a week)*	
	*4. How long per day do you play active games on a weekend day? (… hours; … minutes)*	
Companions for active/non-active gaming	*With whom do you usually play active/ non-active games?*	Specifically developed for the current study^1^
	- *By myself,*	
	- *With my parents,*	
	- *With my brother/sister,*	
	- *With my friends,*	
	- *With somebody else, namely …*	
Game consoles and applications owned	*Which consoles and application do you have at home? (PlayStation 1/2/3; PlayStation Move; PSP (PlayStation Portable); Xbox; Xbox 360; Kinect; (Super)Nintendo; Nintendo Wii; Nintendo DS(i); Gamecube; Gameboy; Dance Dance Revolution; EyeToy; Computer/Laptop; iPad or another tablet)*	Specifically developed for the current study^1^
**Physical activity**		
Sports	*1. Which sports do you play in leisure time?*	Flemish physical activity computer questionnaires [51]
	*2. How often do you play these sports in leisure time? (1–7 times a week, > 7 times a week)*	
	*3. How long do you play these sports when you play them in leisure time (…hours; ..minutes)*	
**Active transport**			
*School*	*1. How do you usually go to school? (bike, walking, train/car/bus/scooter/moped, step/roller-skates/skateboard/wave board)*	Flemish physical activity computer questionnaires [51]	
	*2. How long does it take to go from home to school (one way)? … minutes*		
	*3. Do you go home during lunch break? (yes; no)*		
	*4. On which days do you go home during*		
	*5. Lunch break? (Monday; Tuesday; Wednesday; Thursday; Friday)*		
*Leisure time*	*Weekdays*		
	*6. How long on a weekday do you usually walk in your leisure time to go somewhere (excluding walking to school, work or trainee post)? (0–10; 10–20; 20–30; 30–40;40–50; 50–60 minutes per day; more than one hour per day (… hours and … minutes per day)*		
	*7. How long on a weekday do you usually cycle in your leisure time to go somewhere (excluding walking to school, work or trainee post)? (0–10;10–20; 20–30; 30–40; 40–50; 50–60 minutes per day; more than one hour per day (… hours and … minutes per day)*		
	*Weekend days*		
	*8. How long on a weekend day do you usually walk in your leisure time to go somewhere (excluding walking to school, work or trainee post)? (0–10; 10–20; 20–30; 30–40; 40–50; 50–60 minutes per day; more than one hour per day (… hours and … minutes per day)*		
	*9. How long on a weekend day do you usually cycle in your leisure time to go somewhere (excluding walking to school, work or trainee post)? (0–10; 10–20; 20–30; 30–40; 40–50; 50–60 minutes per day; more than one hour per day (… hours and … minutes per day)*		
**Sedentary screen time**			
TV time	*About how many hours a day do you watch television in a normal week? (excluding school time)*	Flemish physical activity computer questionnaires [51]	
	- *During weekdays: …. hours; …. minutes.*		
	- *During weekend days: …hours; …. minutes*		
Computer time	*About how many hours a day do you spend on the computer (e.g. chatting, internet) in a normal week? (excluding non-active and active gaming)*		
	- *During weekdays: …. hours; …. minutes.*		
	- *During weekend days: …hours; …. minutes*		
**Dietary behavior**			
Consumption of sugar sweetened beverages	Sugar-sweetened beverages were defined as carbonated soft drinks, other non-carbonated sugar sweetened drinks (water-based beverages that contain sugar) and so-called sport and energy drinks (e.g. AA, Extran, Aquarius, Red Bull). Excluding light or diet drinks and fruit juices.	Van der Horst et al. 2008 [52]	
	1. *On how many days a week do you usually drink soda? (1–7 days a week)*		
	2. *If you drink soda, how many soda do you drink on average on one day?*		
	*How many glasses/packages (250 ml)? (none, 1, 2, 3, 4, 5, 6, 7 or more)*		
	*How many cans (330 ml)? (none, 1, 2, 3, 4, 5, 6, 7 or more)*		
	*How many bottles (500 ml)? (none, 1, 2, 3, 4, 5, 6, 7 or more)*		
	*3. On how many days a week do you usually eat cake or candy? (1–7 days a week)*		
	*4. If you eat cake or candy, how many do you eat on average on one day?*		
	*1, 2, 3, 4, 5, 6 or more portions/pieces*		
Consumption of snacks	Savory (fast-food, pizza, fries, chips, nuts).	Van der Horst et al. 2008; Van Assema et al., 2001 [52,53]	
	1. *On how many days a week do you usually eat snacks?*		
	*1-7 days a week*		
	*5. If you eat snacks, how many do you eat on average on one day?*		
	*1, 2, 3, 4, 5, 6 or more portions/pieces*		
	Sweet (candy, candy bars, chocolate, cake, biscuits)		
	1. *On how many days a week do you usually eat cake or candy?*		
	*1-7 days a week*		
	*2. If you eat cake or candy, how many do you eat on average on one day?*		
	*1, 2, 3, 4, 5, 6 or more portions/pieces*		

^1^The questions that were specifically developed for the current study were based on focus groups and/or a previous survey study on active and non-active gaming among adolescents [19,22] and were pilot-tested in gaming adolescents to assure understanding and face validity.

**Table 3 T3:** Process evaluation measures assessed in intervention group

**Process evaluation concepts**	**Items and answering categories**	**Instrument/source**
**1) Adherence to the intervention**		
Usage of Move games	*Did you succeed in playing the move games for at least one hour per week?*	Specifically developed for the current study^1^
	-* Yes, I played the move games for at least one hour per week*	
	- *No, In some weeks I failed to play the move games for at least one hour*	
	- *No, I never succeed in playing the move games for at least one hour per week*	
Reasons for not playing (the minimal of one hour per week)	*Why did you not managed to play the move games for at least one hour per week?*	Specifically developed for the current study^1^
	- *I was too hot*	
	- *I was not allowed by my parents*	
	- *There was somebody else playing on the Move.*	
	- *The move console did not worked properly*	
	- *The move games did not respond well to my movements*	
	- *I think the move games are too tiring*	
	- *I think the move games are boring*	
	- *We have not enough space to play to move games well*	
	- *I had not enough move games*	
	- *I did not have time*	
	- *I think the move games are stupid*	
	- *I had to many other things to do*	
	- *There wasn’t somebody to play with and it is boring to play the games by myself*	
	- *I was injured*	
	- *I rather play non active games*	
	- *Other, namely …*	
**2) Opinion of the move games and the intervention**		
Enjoyment with respect to playing the Move games	*I enjoy playing the Move games (totally disagree (1) – totally agree (7))*	Intrinsic Motivation Inventory (sub scale enjoyment) [54]
	*Playing the Move games is fun to do (totally disagree (1) – totally agree (7))*	
	*I think playing the Move game is boring (totally disagree (1) – totally agree (7))*	
	*Playing the Move games could hold my attention (totally disagree (1) – totally agree (7))*	
	*I would describe playing Move games as very interesting (totally disagree (1) – totally agree (7))*	
	*I think playing the Move games is quite enjoyable (totally disagree (1) – totally agree (7))*	
	*While playing the Move games, I was thinking about how much I enjoyed it (totally disagree (1) – totally agree(7))*	
Most played move game	*Which game did you play most often?*	Specifically developed for the current study^1^
Most enjoying move game	*Which game did you like the most?*	Specifically developed for the current study^1^
Ease of use	*It’s easy for me to learn how the Move games work (totally disagree (1) – totally agree (5))*	Davis, 1989; Hsu & Lu, 2004 [55,56]
	*Playing the Move games is easy for me (totally disagree (1) – totally agree (5))*	
Perceived competence	*I believe I am good in playing Move games (totally disagree (1) – totally agree (5))*	Intrinsic motivation inventory (subscale competence) [54]
	*I think I am better at playing the Move games than other people of my age and gender (totally disagree (1) – totally agree (5))*	
	*I am generally happy with my gaming performance (totally disagree (1) – totally agree (5))*	
Perceived physical exertion of playing move games	*How would you rate the intensity level of playing the Move games?*	Specifically developed for the current study^1^
	- *Light, little body movements are required while playing on the Move, and my breath rate does not accelerate;*	
	- *Moderate, I move my body quite a lot while playing on the Move and my breath rate accelerates a little bit;*	
	- *Hard, I have to move a lot and fast, I get out of breath and I am sweating during playing on the Move*	
Opinion on the amount of provided Move games	*What do you think about the amount of provided move games? (too little - exactly right - too much)*	Specifically developed for the current study^1^
Self purchased move game	*Did you bought, received, borrowed or downloaded other Move games in addition to the games we provided you?*	Specifically developed for the current study^1^
**3) Game context**		
Move game companion	*With whom do you usually play the Move games? (by myself, with my parents, with my brother/sister, with my friends, with somebody else, namely …)*	Specifically developed for the current study^1^
Location of PlayStation move console	*Where was the PlayStation PlayStation®Move located most of the time? (Living room, my own bedroom, my brother’s or sister’s bedroom, in the attic, in a shared game room, somewhere else, namely …)*	Specifically developed for the current study^1^
**4) Potential adverse effects**		
Occurrence of injuries because of playing with the move games	*Did you hurt or injured yourself during playing with the Move? (yes; no)*	Specifically developed for the current study^1^
	*What kind of injury occurred during game play? (bruise; graze; strained muscles or tendons; bruised something (e.g. ankle, wrist); broke something (e.g. leg, wrist, arm); some other injury, namely ….)*	
**5) Activity replacement**	*Can you think back about the time you did not have the Move games yet, what did you do with the time you now spend on active gaming?*	Simons et al., (2012) [45]
**6) Intention to continue playing the move games**	*1. I intend to continue playing the Move games;*	Based on Theory of Planned Behavior [57]
	*2. I expect to continue with playing the Move games (totally disagree (1) – totally agree (5)).*	

^1^The questions that were specifically developed for the current study were based on focus groups and/or a previous survey study on active and non-active gaming among adolescents [19,22] and were pilot-tested in gaming adolescents to assure understanding and face validity.

##### Time spent active and non-active gaming (T_0_, T_1m_, T_4m_, T_10m_)

To assess time spent active and non-active gaming, questions are formulated based on existing and validated questionnaires for adolescents asking about frequency and duration, for school and weekend days separately [50,58]. Adolescents can indicate the duration by selecting one of four categories (<30 minutes, 30–60 minutes, 1–2 hours, and >2 hours). Average values are calculated for every category (<30 minutes = 15 minutes; 30–60 minutes = 45 minutes; 1–2 hours = 90 minutes; >2 hours = 150 minutes) and multiplied by the frequency, resulting in total hours per week spent on active and non-active games separately.

##### Other physical activity and sedentary screen time (T_0_, T_1m_, T_4m_, T_10m_)

Assessment of physical activity and sedentary screen time occurs by determining the frequency and the amount of time spent on different leisure-time sedentary and physical activities based on the validated Flemish Physical Activity Computer Questionnaires (FPACQ) [51]. The FPACQ assesses physical activity and sedentary behavior in multiple domains: school activity (physical activity and sports participation at school excluding physical education lessons), active transport (transportation for example by bike, and walking (for both school and leisure time), non-active transport (transportation for example by car or bus (for both school and leisure time) leisure time sports participation, and sedentary activities (watching television and computer activities). For the current study we focus on the domains active transport and leisure time sports participation for physical activity. Physical activity outcomes are leisure time sport behavior (MET*hours per week), active transport to school (minutes per week) and walking and cycling in leisure time (minutes per week). Sports participation in MET*hours per week is calculated by multiplying the reported hours per week by their corresponding MET values according to the compendium of MET values [59]. For sedentary screen time we focus on computer time (hours per week) and TV time (hours per week). Computer time includes all activities on a computer such as chatting and surfing on the internet, except playing computer games. Both computer and TV time are assessed separately for week- and weekend days.

##### Consumption of snacks and sugar sweetened beverages (T_0_, T_1m_, T_4m_, T_10m_)

Consumption of sugar-sweetened beverages is assessed using questionnaires by Van der Horst et al. [52]. Consumption of sugar-sweetened beverages includes consumed glasses, cans and bottles of carbonated and non-carbonated soft drinks, lemonade, and sport and energy drinks. Diet sodas and juices are not assessed. Total consumption of sugar sweetened beverages is expressed in liters per day, and is calculated according to Dutch standard serving sizes (1 glass = 200 ml, 1 can = 330 ml, 1 bottle = 500 ml). Consumption of snacks is assessed using items from a validated questionnaire [52,53]. Snacks are classified as savory (e.g. fast-food, pizza, fries, chips, nuts) or sweet (e.g. candy, candy bars, chocolate, cake, biscuits) eaten between the main meals, and not as side servings at main meals. Quantity of consumed snacks is obtained by determining amount of “snack days” and amount of snacks consumed per “snack day”. These questions are combined into a single score for the amount of portions snack intake per week.

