### Statistical analyses

First descriptive analyses are performed and data are checked for a normal distribution. Subsequently, control group and intervention group are described on baseline for demographics and outcome measures. Next, the effects of the intervention on all outcomes are evaluated by multilevel analyses. In the primary analyses, we analyze those participants which have at least one follow-up measurement in the groups they were randomized to. As a sensitivity analyses we will also impute follow-up measurements for persons with only a baseline measurement using multiple imputation with chained equations (intention to treat). Two models are constructed for each outcome measure: *model 1* adjusts for the baseline value of the outcome measure; and *model 2* additionally adjusts for demographics (age, sex, ethnicity and adolescent educational level) that are expected to associate with the outcome [3-5]. Second, analyses are performed according to the per protocol principle including the participants in the intervention group who played the Move games at least one hour per week. Adherence to protocol will be defined for each follow-up measurement separately, based on the question in the questionnaire assessing use of Move games (in hours per week) at T_1m_, T_4m_ and T_10m_. Again, two models are constructed for each outcome measure: *model 1* adjusts for baseline outcome measure; and *model 2* adjusts for demographics (age, sex, ethnicity and adolescent educational level) that are expected to associate with the outcome [3-5].

Additionally, a sensitivity analyses is performed by constructing all the models excluding the more extreme values on sedentary screen time (e.g. > 12 hours per day of non-active time). Further, if feasible (i.e. if the number of participants allows), explorative analyses are performed to check whether sex, age, adolescent educational level and ethnicity are effect modifiers, using a significance level of 0.10 because the study is not powered for detecting effect modification.

For the process evaluation, descriptive statistics are used describing the use of the Move games based on the Move game calendar over the ten months intervention period and the process evaluation measures. All statistical analyses are performed using IBM SPSS Statistics version 21 and statistical significance level is set at p < 0.05 for detecting main intervention effects and p < 0.10 for detecting effect modifiers.

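### Scoring rules for beverage intake and gaming time, two self-reported secondary outcomes, contradict the questionnaire items printed in Table 2

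*Protocol article*

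**What the plan says.** All places are in the protocol article. The abstract lists time spent on active and non-active games and consumption of sugar-sweetened beverages among the secondary outcomes.

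**Beverages.** The section on consumption of snacks and sugar sweetened beverages expresses intake in litres per day and converts servings with "1 glass = 200 ml, 1 can = 330 ml, 1 bottle = 500 ml". The items under Dietary behavior in Table 2 read "How many glasses/packages (250 ml"), "How many cans (330 ml") and "How many bottles (500 ml"). Can and bottle agree with the conversion; the glass does not.

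**Gaming time.** The section on time spent active and non-active gaming says "Adolescents can indicate the duration by selecting one of four categories (<30 minutes, 30–60 minutes, 1–2 hours, and >2 hours"). It scores these as 15, 45, 90 and 150 minutes and multiplies by frequency, with school days and weekend days asked separately. Table 2, under Gaming aspects and behavior, prints the duration item ("How long per day do you play non-active games on a weekday") with blanks for hours and minutes and no categories.

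**Active-gaming items.** In the same table, the second and third active-gaming items are the same weekend frequency question. No item asks how long active games are played on a weekday.

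**The concern.** Each pair of statements describes one instrument in two incompatible ways, and nothing in the article reconciles them. It does not say, for example, that open answers are sorted into categories afterwards. An analyst following the text would apply a 200 ml constant to a serving that Table 2 shows as 250 ml, and a category score to what Table 2 shows as an open answer.

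At stake are the absolute scale of beverage intake, which is reported in litres, and the ability to see change in heavy gamers. The intervention asks for only about one hour per week of substitution, so a coarse, capped duration score suits the intended change poorly. The Blinding section says the analyses are not blinded, which is a further reason to settle the scoring beforehand.

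**Working it through.** The article gives no derived figure to reproduce, so the check sets items against scoring rules and follows the arithmetic.

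**1. Glass size.** Inputs: 200 ml (text), 250 ml (Table 2); can 330 ml and bottle 500 ml (both places).

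| Daily intake | Scored at 200 ml | At 250 ml as printed | Shortfall |
|---|---|---|---|
| 3 glasses | 0.60 L | 0.75 L | 1 − 0.60/0.75 = 20% |
| 2 glasses + 1 can | 0.73 L | 0.83 L | 1 − 0.73/0.83 = 12% |
| 1 glass + 1 can | 0.53 L | 0.58 L | 1 − 0.53/0.58 = 8.6% |
| 1 glass + 1 can + 1 bottle | 1.03 L | 1.08 L | 1 − 1.03/1.08 = 4.6% |
| 1 can + 1 bottle | 0.83 L | 0.83 L | 0% |

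A between-group difference in glasses shrinks by the same 20%, because every glass is multiplied by 200/250.

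**2. Gaming duration.** Inputs: the four category scores (text); the typical durations of 65 minutes on a school day and 80 minutes on a weekend day (Background).

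- Midpoints: (0 + 30)/2 = 15, (30 + 60)/2 = 45 and (60 + 120)/2 = 90 reproduce. The top category has no upper limit. Its 150 is a midpoint only if it ends at 2 × 150 − 120 = 180 minutes.
- Weekly ceiling: 7 × 150/60 = 17.5 hours. Open answers have no such ceiling.
- Single days: 65 minutes scores 90 (90/65 − 1 = +38%); 240 minutes scores 150 (150/240 − 1 = −38%, rounded from 37.5%).
- Change above the cap: a fall from 5 to 4 hours per day scores 150 both times, a recorded change of zero.
- Weekly total at the Background durations, assuming play on all seven days: open answers give (5 × 65 + 2 × 80)/60 = 8.1 hours; categories give (5 × 90 + 2 × 90)/60 = 10.5 hours.

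The two formats therefore give different data, not two descriptions of the same data.

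**3. Active-gaming items.** Weekly time is weekday frequency × weekday duration + weekend frequency × weekend duration. Table 2 supplies the first, third and fourth terms, the third twice, and lacks the second. The weekly total cannot be formed from the items as printed.

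**The case against.** **The outcomes may not be mis-scored at all.** A reader might infer that the data are certainly scored wrongly. The document does not support that, because it does not show what was administered. If the fielded item showed a 200 ml glass, the text is right and Table 2 is the misprint; the same holds if closed duration categories were used. This objection stands: the contradiction is certain, while the 20% depends on Table 2 being the fielded version.

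**The outlier analysis is not affected.** A reader might also infer that the planned sensitivity analysis "excluding the more extreme values on sedentary screen time (e.g. > 12 hours per day of non-active time") cannot work if gaming is capped at 150 minutes. That does not follow. The rule is stated for sedentary screen time, which the article measures as TV and computer time without computer games, both recorded in open hours and minutes. Values above 12 hours remain possible under either gaming format.

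**Both arms are scored alike.** This stands. Neither error favours one arm, and for adolescents who drink only from glasses a wrong constant rescales the data without changing a test statistic. It does not rescue an outcome reported in litres, nor mixed intake, where glasses are underweighted relative to cans and bottles.

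**Category scores largely recover group means.** This stands in part. Take lognormal daily durations with mean 65 to 80 minutes and a coefficient of variation of 0.6 to 1.0 (the shape and the variation are assumptions). A cut of 12 minutes per day then leaves 68% to 75% of scores unchanged, yet the mean score falls by 9.5 to 12.2 minutes, about 0.8 to 1.0 of the true change. Only 8% to 18% of days exceed two hours. Because duration is multiplied by frequency, playing on fewer days is also captured above the cap. The loss is thus concentrated in heavy gamers who shorten their sessions.

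**The duplicated item is a copying slip.** Very likely: the parallel non-active list shows what was meant. It still needs correcting, because Table 2 is the only place where the items are set out.

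**The reach is limited.** Hypothesis 2 also covers TV and computer time, and hypothesis 3 also covers snacks; none of these is touched here.

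**Conclusion.** The concern holds as an unreconciled contradiction between scoring rules and items for two self-reported secondary outcomes.

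- **Beverages:** if Table 2 was administered as printed, the glass component and any group difference in it are 20% too low. The total is between 0% and 20% too low depending on the mix of containers.
- **Gaming time:** if the category rule is applied, daily duration is capped at 150 minutes, and changes in duration above two hours per day leave no trace.
- **Active gaming:** the weekly total cannot be computed from the printed items.

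The consequences are wrong scale and lost information, not bias towards one arm. The anthropometric primary outcomes and the sample size are untouched. The point should be settled before analysis but does not threaten the trial's main conclusion.

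**What to change.** Before analysis, check the online questionnaire as fielded, then make Table 2, the text and the scoring agree with it:

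1. Score a glass or package at the volume shown to the adolescent: 250 ml if Table 2 is right. If the item showed 200 ml, correct Table 2 instead.
2. If gaming duration was collected in open hours and minutes, use those values and remove the category recoding from the text. If categories were used, correct Table 2 and report the 150-minute cap with the results.
3. Replace the duplicated active-gaming item in Table 2 with the weekday duration item, after confirming that it was asked.

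The cost is a check of the questionnaire, corrected text and, at most, a changed glass constant and removal of a recoding step. No new data are needed if weekday duration was asked. If it was not, weekly active gaming time cannot be recovered from the questionnaire, and the article should say so. No change of statistical model is required.
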